#### Sample size

The sample size calculation is based on the sleep component `sleep efficiency´. A previous RCT [37], using PSG as measurement of sleep, examined the effect of a non-pharmacological intervention (cognitive behavioral therapy) on sleep disturbances in patients with insomnia and found a mean sleep efficiency of 81.4% (SD 7.4). The normal value for sleep efficiency is >85%. Thus the aim for the patients in the exercise intervention was to achieve a sleep efficiency of at least 86%. On this basis, and with a significance level of α = 5% and a power of 80%, it is estimated that 36 patients should take part in this trial. A drop-out rate of 20% is expected, which means that 44 patients are included, of which 22 are randomly assigned to the intervention group and 22 to the control group.

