#### Trial endpoints

##### Data collection

Objective physiological as well as patient reported outcomes are collected at baseline and at the end of the intervention (6- 8 weeks).

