### Statistical analyses

Continuous variables, i.e., sleep, cardiorespiratory fitness, physical function, pain, fatigue, depressive symptoms and health-related quality of life will be presented as either means with corresponding 95% confidence limits or as medians and interquartile range (IQR). The primary and secondary endpoints will be reported as a two-sample t-test comparing change scores in the two randomized groups. The primary outcome variables in the regression model will be sleep parameters. The regression model will allow control for the baseline value of the trial endpoints and other confounding variables that may impact changes in sleep parameters (e.g. age and gender). Categorical data, i.e., single questionnaire items, will be reported as proportions and compared across randomized groups using chi-squared tests or logistic regression. Significance level will be set at 0.05. All tests will be two-tailed. The primary analysis will compare changes in the intervention vs. the control group using the intention-to-treat principle including all available data. Missing observations will be handled according to the missing at random assumption. The secondary analysis will include only patients attending at least 14 exercise sessions (80%) out of the prescribed 18 (i.e. per protocol analysis). Finally, correlations will be performed to examine the dose-response relation between changes in the primary outcome (sleep) and cardiorespiratory fitness. Data entry will be undertaken using a secure web server and statistical analysis will be performed using Statistical Analysis Systems (SAS) version 9.3.

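### The endpoints are tied to a change-score t-test, which need not be valid under the stated missing-at-random assumption; the baseline-adjusted regression named beside it should be primary

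*Protocol article*

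**What the plan says.** The protocol article's section on statistical analyses makes four statements that bear on this point:

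- The test: "The primary and secondary endpoints will be reported as a two-sample t-test comparing change scores in the two randomized groups".
- A second model, with sleep parameters as the outcome: "The regression model will allow control for the baseline value of the trial endpoints and other confounding variables that may impact changes in sleep parameters". Age and gender are given as examples of the other variables.
- The analysis set: the primary analysis compares changes between the arms "using the intention-to-treat principle including all available data".
- The missing-data assumption: "Missing observations will be handled according to the missing at random assumption".

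The section does not say which of the two analyses, t-test or regression, is the primary one. Only the t-test is linked by name to the primary and secondary endpoints.

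Elsewhere, the data collection section gives two measurement times, baseline and the end of the intervention at 6 to 8 weeks, so there is a single follow-up polysomnography. The sample size section states "A drop-out rate of 20% is expected" and randomises 44 patients to obtain 36.

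**The concern.** A patient who leaves before the second polysomnography has no change score. Taken as written, the t-test drops that patient and also the baseline recording already made. What is left is a comparison of completers, whereas the text promises all available data and an analysis that is valid under MAR.

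This matters because change depends on baseline. Through regression to the mean, patients with low baseline sleep efficiency tend to rise and those with high values tend to fall, whatever the treatment. If the completers in one arm started from a different baseline level than those in the other, the t-test counts part of that regression as treatment effect. Only one arm is asked to attend 18 supervised sessions with high-intensity blocks, while controls carry on as usual, so a different pattern of loss in the two arms is plausible. With both analyses in the text and neither designated primary, the headline result could come from the one that fits the stated assumption less well.

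**Working it through.** **Inputs from the protocol article (sample size section).** Reference mean sleep efficiency 81.4%, SD 7.4; target in the exercise arm at least 86%; 36 patients needed; 20% drop-out; 44 randomised, 22 per arm. The effect used below is 86 − 81.4 = 4.6 points.

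**Inputs that are assumed.** The article gives neither the correlation r between baseline and follow-up nor any drop-out model. I take r = 0.3, 0.5 and 0.7, equal SDs at both times, a constant treatment effect, 20% loss in each arm, and a logistic dependence of loss on baseline with a slope of about 1 per SD.

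**Step 1: patients lost to the t-test.** The plan's 44 reproduces as 36 × 1.2 = 43.2, rounded up to two equal arms. At 20% drop-out, 44 × 0.20 = 8.8, so about 9 patients have no change score; 44 × 0.80 = 35.2, so about 35 do.

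**Step 2: formula for the bias.** Let Y0 be baseline, Y1 follow-up, A the arm (1 = exercise), μ the common baseline mean and δ the true effect, with

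E(Y1 | Y0, A) = μ + δA + r(Y0 − μ).

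Then E(Y1 − Y0 | Y0, A) = δA − (1 − r)(Y0 − μ). If loss depends only on arm and baseline, this also holds among completers. With m1 and m0 the completers' mean baselines in the exercise and control arms, the t-test estimates

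δ − (1 − r)(m1 − m0), so bias = −(1 − r)(m1 − m0).

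The bias is zero when m1 = m0. That covers loss completely at random, and loss that depends on baseline in the same way and at the same rate in both arms. Regression of Y1 on A and Y0 conditions on Y0 and so recovers δ.

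**Step 3: size when loss depends on baseline in the exercise arm only.** Suppose patients with low sleep efficiency are more often lost, with slope −1 per SD. An intercept of −1.65 gives 20% loss overall. Averaging the standardised baseline over those retained gives +0.173 SD, so m1 − m0 = 0.173 × 7.4 = 1.28 points. Then:

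| r | −(1 − r) × 1.28 | Simulated bias, t-test | Simulated bias, baseline-adjusted |
|---|---|---|---|
| 0.3 | −0.90 | −0.88 | 0.02 |
| 0.5 | −0.64 | −0.66 | −0.01 |
| 0.7 | −0.38 | −0.40 | −0.01 |

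The simulations used 400,000 patients per arm. If instead patients with high baseline values are lost, the sign reverses: +0.87, +0.67 and +0.41.

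**Step 4: other patterns.**

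- Slope 1.1, 22 per arm, 6,000 simulated trials: the t-test averages 3.57, 3.84 and 4.18 against a true 4.6 (bias −1.03, −0.76, −0.42). The baseline-adjusted analysis averages 4.60, 4.57 and 4.60.
- Slope 0.7, same design: the t-test averages 3.93, 4.19 and 4.35 (bias −0.67, −0.41, −0.25).
- Opposite dependence in the two arms, slope 1 (large sample): −1.82, −1.28 and −0.73.
- Completely random loss, or the same dependence in both arms (large sample): within 0.03 of zero at every r.

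In all large-sample scenarios the baseline-adjusted regression on the same completers stayed within 0.02 points of zero bias.

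**The case against.** A reader might infer that the plan contradicts itself outright: that its only analysis is a complete-case t-test, and that the primary result will be biased. The document does not support that reading, for three reasons.

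- The t-test is not the only analysis. The baseline-adjusted regression stands in the same paragraph, and with one follow-up visit it is valid on completers if loss depends only on arm, baseline and the other covariates in the model. This stands, and it narrows the point to which analysis is primary.
- Complete-case use is inferred. A change-score t-test can be run after multiple imputation, and the method that implements MAR may be set out in a full protocol or analysis plan that is not at hand. Its absence from an article is no finding. This also stands, and it is why the conclusion is conditional on no imputation.
- The bias is not automatic, its sign is not fixed, and it is modest against the noise. With 18 per arm the standard error of the change difference is 7.4 × √(2(1 − r)) × √(2/18), or 2.9, 2.5 and 1.9 points at r = 0.3, 0.5 and 0.7. The biases in the table above are about 0.2 to 0.3 of that. A slope of 1.1 per SD, an odds ratio of about 3, is a strong dependence.

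What the objection does not remove is that the text attaches the endpoints to the t-test and gives the regression no rank. Choosing between two named analyses is not a detail that can safely wait until the data are seen.

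**Conclusion.** The point holds in a limited form. The analysis that the article links to its endpoints does not by itself have the property the article claims for the primary analysis. Unless values are imputed, it leaves out about 9 of 44 randomised patients, and it can be biased under MAR when drop-out depends on baseline sleep differently in the two arms.

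Under one-arm dependence with a slope of 1.0 to 1.1 per SD, the bias is roughly 0.4 points at r = 0.7 and 0.9 to 1.0 points at r = 0.3. That is about 9% to 22% of the assumed 4.6 (0.4/4.6 and 1.0/4.6), in either direction. These sizes rest on assumed correlations and drop-out slopes, not on figures in the article. The statement that baseline adjustment removes the bias rests on loss depending only on arm and the adjusted covariates, and on the follow-up being linear in baseline.

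**What to change.** State in the statistical analyses section that the primary analysis of sleep efficiency, the component on which the sample size is based, is the baseline-adjusted comparison of the randomised arms. Two forms are suitable:

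- ANCOVA of follow-up sleep efficiency on arm and baseline. It uses completers but is valid under MAR given those terms.
- An equivalent linear mixed model with both polysomnography time points as outcomes, the baseline means constrained equal across arms, and the group difference at follow-up as the effect. This also includes the drop-outs' baseline recordings, so all 44 randomised patients enter and the promise of all available data is met.

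Demote the change-score t-test to a descriptive or supportive result.

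More than this is not required. Imputation using session attendance would be awkward because controls have no sessions to attend, and a delta-adjusted sensitivity analysis is optional.

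The cost is a sentence or two of text and little or no extra programming in the SAS version already named. No new data are needed, and the article says recruitment was still under way when it was submitted.

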### Qualitative investigation and methods

Qualitative, semistructured interviews will be held with purposefully selected sample of patients from the intervention group. These interviews will highlight patients’ experience with intermittent aerobic exercise including potential changes in pain, fatigue and sleep.

### Ethical considerations and confidentiality

The trial follows international ethical guidelines of informed consent in clinical trials. Patients receive written and verbal information about the trial to ensure they are able to give informed consent. Participation is voluntary and patients can withdraw their consent at any time during the trial with no consequences for their treatment. Research ethics approval to conduct this trial was obtained though the Regional Ethics Committee (Journal No. H-1-2012-151) and the trial has been registered in http://www.clinicaltrials.gov (NCT01966835). The trial is approved by the Danish Data Protection Agency (Ref. No. 711-1-08). All information collected during the course of the trial is kept confidential in accordance with Danish Data Protection Agency rules.

## Discussion

The present trial will contribute with empirical evidence to the field of exercise and sleep that is currently characterized by premature empirical results but with significant potential as a non-pharmacological approach for improving sleep and with several aspects beneficial to health. The mechanisms of how physical exercise may reduce poor sleep are yet unknown. One hypothesis may be that sleep decrease symptoms of depression [48], another is that exercise engages with the two-process model of circadian and homeostatic regulation [49] or stimulates the restorative function during sleep and triggers an increase in body temperature [50,51]. The post-exercise drop in temperature may promote sleep onset latency and slow-wave sleep.

The present trial is superior to others within the field of exercise and sleep in three ways. Firstly, we have chosen the golden standard method for measuring sleep (i.e. PSG). In comparison, the majority of previous studies with the aim of improving sleep through physical exercise interventions have relied on self-reported instruments such as PSQI and only one trial has used polysomnographic assessment to measure sleep objectively [35].

Secondly, whereas current exercise trials typically apply continuous moderate intensity aerobic exercise training, we have chosen to apply aerobic intermittent training. While regular continuous aerobic exercise is known to improve a wide range of health outcomes, including cardiorespiratory fitness in both healthy people and clinical populations, aerobic intermittent training of shorter duration may result in an equal or superior improvement in fitness [36].

Finally, this is the first trial within the field of RA to evaluate the effect of aerobic intermittent training on improvement in sleep quality and sleep disturbances. The detailed information collected in this trial regarding the exact completed adherence to the exercise regime (including intensity (watt) as well as pulse monitoring during each training block and interval, and objective measured sleep duration, sleep stages, and sleep quality) is expected to provide important experimental results that can contribute with evidence of both aerobic intermittent training and poor sleep, including causal interactions between the two.

### Trial status

At the time of manuscript submission the patients are being recruited to the trial.
